### Secondary Outcome Measures

Secondary outcomes include balance and aerobic endurance measures that are assessed pre- (T1) and post-(T2) intervention by the following tests:

1) The **Postural Stability Test** measures balance postural control by the body sway in upright standing. The participants are instructed to stand barefoot as still as possible on a force platform in a standardized stance, their feet close together with their hands crossed behind their back (50). Five 30-s eyes-open (EO) and eyes-closed (EC) assessments are conducted for each participant. CoP and ground reaction force data are collected at a frequency of 100 Hz with a single Kistler 9,287 force platform (Kistler Instrument Corp., Winterthur, Switzerland). Balance control is evaluated using both the traditional measures of CoP postural sway (e.g., ML sway range, AP sway range, mean sway velocity, and mean sway area), and the Stabilogram-Diffusion Analysis (SDA) parameters for ML and AP directions: Critical time (Ct), Critical displacement (Cd), and the short-term (Ds) and long-term (Dl) effective diffusion coefficients. This was described in detail by Collins and De Luca (51, 52). The data are extracted from the CoP trajectories using a code written in MatLab (Math Works Inc., Cambridge, MA, USA). The ICC for the CoP sway parameters are excellent in the EC condition: ML sway (ICC=0.933), AP sway (ICC=0.946), sway area (ICC=0.710), sway length (ICC=0.945) (53), and fair-to-good reliability to the SDA parameters: Ds (ICC=0.79), Dl (ICC=0.50), Cd (ICC=0.66), Ct (ICC=0.63) (54). In the narrow-base standing condition, the ML sway range and the mean sway velocity (55), as well as the Cd and Ds (56) are predictive variables for falls (55, 56) and the severity of fall-related injury (50).

2) The **Voluntary Step Execution test** measures anticipatory (proactive) balance control by the ability to perform a quick step. Participants stand on a single force platform with their feet abducted 10° and their heels separated medio-laterally by 6 cm. They are instructed to voluntarily step (50–60 cm long) as quickly as possible following a somatosensory cue given randomly on **one** of their heels (57, 58). CoP movement and ground reaction force data are collected from the Kistler 9287 force platform. A total of **eight** trials are conducted in single-task and dual-task conditions (while performing the modified Stroop task): four forward and four sideways. The average result across task conditions are used for statistical analysis. Participants view an “X” displayed on a screen in front of them. Specific temporal events are extracted from the step execution data: (a) reaction time; (b) foot contact time; (c) preparation time; and (d) swing time (57, 58). The ICC values for intra-tester reliability for older adults are good to excellent for all the step parameters across all task conditions (0.62–0.88) except for the swing time variable (0.32–0.64) (59). The foot contact time and the initiation phase were able to predict future falls (60) and injury from fall (58).

3) The **Berg Balance Scale** (BBS) is a clinical functional balance instrument that assesses balance and fall risk. It is a 14-item performance-based measure of functional balance skills. Each task is scored 0–4 on an ordinal scale, and the total score ranges are 0–56. A higher score represents better balance (61). It highly correlates with other functional measurements. A score <45 indicates individuals at greater risk of falling (62).

4) The **Six-Minute Walk Test** (6MWT) is a sub-maximal test of aerobic capacity measuring the maximum distance that a person can walk in 6 min (63). We use this measure to control for the endurance component of the pedaling training.

5) The **Late Life Function and Disability Instrument** (LLFDI) is a self-reported function measuring difficulty in performing basic and advanced daily physical tasks (64).

6) The **Falls Efficacy Scale-International** (FES-I) evaluates fear of falling while performing indoor and outdoor social and physical daily activities (65).

#### Assessing Upper Body Balance Reactions During Training

During each training session of the experimental PerTSBR group, the data of skeleton joint identification that was obtained by the Microsoft Kinect^KM^ camera is recorded for post-training analysis. Trunk and upper body balance recovery responses are assessed for each of the perturbations by the physiotherapist/trainer using kinematic graphs and a movie of the trainee riding the PerStBiRo system. This data helps the physiotherapist to analyze the trainee's balance behavior during the perturbations and to determine how to proceed with the training program in the next sessions (see Figure 3).

### Data Management

At the baseline assessment (T1), each participant receives a computer-generated personal identification code. All data are collected and stored anonymously with this personal code, and the data are the responsibility of the principal investigator (IM). Participants' medical and personal information obtained in this study are considered confidential, and disclosure to third parties prohibited. Electronic data are stored on secure institutional servers immediately after both assessment sessions. Hard copies of files are stored in locked cabinets in our laboratory. Each participant has an electronic folder, as well as a hard-copy folder with their own personal code consisting of raw and analyzed data, test results, and questionnaires from pre- and post-training assessments. The names and phone numbers of participants are only be accessible to the research team for contact purposes. To ensure protection of participants' personal information, the data collected during the study will be kept confidential, and saved and stored on secure servers for 10 years, are password protected, and will not be shared with anyone outside of the study unless required by law. The data will be deleted from the servers after 10 years. Hard files containing de-identified data and consent forms are stored separately from other data and in locked cabinets in our laboratory. Only researchers from the research team allowed access to the data for the purpose of this study are provided with the password to the file containing identifiers and/or the keys to the locked cabinet/office.

### Sample Size Estimation

Sample size requirements were calculated using PS power calculation software (66). Because the aim of the study is to examine the effect of perturbation-based bicycle training on various aspects of balance control, well-known parameters that reflect reactive, proactive, and standing postural balance control were selected. Calculations were performed separately to determine sample size requirements based on a single-step threshold in standing (reactive balance), voluntary step execution (i.e., foot contact time) (proactive balance), and ML postural sway (standing postural control), all reflective of unsteadiness in balance control between older and younger adults (13, 14, 50, 55, 58, 67, 68) and between fallers and non-fallers (13, 15–21, 55–58, 60). Type I error probability of 0.05 and Type II error probability of 0.2 was applied for the three two-sided test calculations. Based on our preliminary results, the compensatory single-step threshold in standing was 10.8 cm of lateral translation in older adults with bicycle riding habits compared to 7.9 cm in age- and gender-matched controls [data in processing], the ML postural sway in EO was 30.6 mm in older adults with bicycle riding habits compared to 38.8 mm in controls (31), and the step execution times (i.e., foot contact time) in single-task condition of older bicyclists were 104 ms less than those of the controls (921 vs. 1,025 ms) (30). Using net reduction values (2.9 cm, 8.2 mm, and 104 ms, respectively) in combination with the initial variance estimates (standard deviations of 3.45 cm, 7.8 mm, and 134 ms, respectively), it was determined that 27 participants per group would be required. To account for reported attrition rates of about 25% in studies involving older adults (69), we decided to include about 34 participants in each group for a total of 54 (27 × 1.25 = 34).

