## Abstract

**Background:** Falls are the leading cause of fatal and non-fatal injuries among older adults. Perturbation-Based-Balance Training (PBBT) is a promising approach to reduce fall rates by improving reactive balance responses. PBBT programs are designed for older adults who are able to stand and walk on a motorized treadmill independently. However, frail older adults, whose fall rates are higher, may not have this ability and they cannot participate. Thus, there is a critical need for innovative perturbation exercise programs to improve reactive balance and reduce the fall risks among older adults in a wider range of functioning. Trunk and arms are highly involved in reactive balance reactions. We aim to investigate whether an alternative PBBT program that provides perturbations during hands-free bicycling in a sitting position, geared to improve trunk and arm reactive responses, can be transferred to reduce fall risks and improve balance function among pre-frail older adults.

**Methods:** In a single-blinded randomized-controlled trial, 68 community-dwelling pre-frail older adults are randomly allocated into two intervention groups. The experimental group receives 24-PBBT sessions over 12-weeks that include self-induced internal and machine-induced external unannounced perturbations of balance during hands-free pedaling on a bicycle-simulator system, in combination with cognitive dual-tasks. The control group receives 24 pedaling sessions over 12-weeks by the same bicycle-simulator system under the same cognitive dual-tasks, but without balance perturbations. Participants' reactive and proactive balance functions and gait function are assessed before and after the 12-week intervention period (e.g., balance reactive responses and strategies, voluntary step execution test, postural stability in upright standing, Berg Balance Test, Six-meter walk test, as well as late life function and fear of falling questionnaires).

**Discussion:** This research addresses two key issues in relation to balance re-training: (1) generalization of balance skills acquired through exposure to postural perturbations in a sitting position investigating the ability of pre-frail older adults to improve reactive and proactive balance responses in standing and walking, and (2) the individualization of perturbation training to older adults' neuromotor capacities in order to optimize training responses and their applicability to real-life challenges.

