### Participants

A convenience sample of 68 community-dwelling older adults will be recruited (see sample size estimation below). Eligibility criteria are: 70 years of age or older, ability to walk independently without assistive devices, independence in daily living activities, and provision of a medical waiver signed by their primary care physician allowing participation in physical training that requires pedaling on a stationary bicycle two or three times a week. After completing a medical history questionnaire via an in-person interview at enrollment, volunteers are excluded if they suffer from: (a) ischemic heart disease which restricts exercise, (b) chronic obstructive pulmonary disease, (c) uncontrolled blood pressure, (d) severe vision problems (blindness), or (e) cognitive impairment, scoring <24 on the Mini-Mental State Examination. Further exclusion criteria include: (f) a period <1 year after hip or knee replacement surgery or after fractures of the lower extremities, (g) amputation of a lower limb, (h) neurological diseases or after a stroke, and (i) inability to ambulate independently, and/or (j) weight > 120 kg (exceeds safety harness weight limits). The study was approved by the Helsinki ethics committee at Barzilai Medical Center, Ashkelon, Israel (BARZI0104).

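### The closing sentence of the sample-size section has two arithmetic errors: 34 per group is 68 in total, not 54, and multiplying 27 by 1.25 covers about 20% attrition, not 25%

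*Protocol article*

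**What the plan says.** Sample Size Estimation (protocol article) runs three calculations: single-step threshold in standing, medio-lateral postural sway, and foot contact time in voluntary stepping. On error rates it states "Type I error probability of 0.05 and Type II error probability of 0.2 was applied for the three two-sided test calculations". The differences are given as "Using net reduction values (2.9 cm, 8.2 mm, and 104 ms, respectively") and the variability as "standard deviations of 3.45 cm, 7.8 mm, and 134 ms, respectively". The result is that "it was determined that 27 participants per group would be required".

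The attrition allowance follows, introduced by "To account for reported attrition rates of about 25% in studies involving older adults", and the section concludes "we decided to include about 34 participants in each group for a total of 54 (27 × 1.25 = 34").

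Elsewhere the planned size is 68. The Abstract has "68 community-dwelling pre-frail older adults are randomly allocated into two intervention groups". Participants has "A convenience sample of 68 community-dwelling older adults will be recruited" and refers the reader to the sample-size section for the reason. The randomization section specifies blocks that give equal group sizes.

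Statistical Analysis lists the single-step threshold among the primary outcomes and foot contact time among the secondary ones. It plans a repeated-measures ANOVA with last observation carried forward for those who do not finish.

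**The concern.** The section that should justify 68 ends on 54. A reader comparing achieved with planned enrolment meets a figure that disagrees with the Abstract, with Participants and with the 34 per group in the same sentence.

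The allowance also misses its own purpose. It is meant to leave 27 per group after a loss of about 25%, but adding 25% to the required number and then losing 25% of the larger number does not return to the start. At stake are the accuracy of a core design figure and how much attrition the planned size can absorb.

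**Working it through.** **Inputs** (all from Sample Size Estimation): two-sided alpha 0.05; power 0.80; differences 2.9 cm, 8.2 mm and 104 ms; standard deviations 3.45 cm, 7.8 mm and 134 ms; attrition about 25%. The section does not name the test. I take a comparison of two independent means and show both the normal approximation and the t-test.

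**Step 1: reproduce the 27.** Standardised difference d = difference / SD. Normal approximation: n per group = 2 × (1.960 + 0.842)² / d² = 15.70 / d², rounded up. The t-test value solves the noncentral t power equation.

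| Variable | d | n, normal | n, t-test |
|---|---|---|---|
| Single-step threshold | 2.9/3.45 = 0.841 | 22.2, so 23 | 23.2 |
| Medio-lateral sway | 8.2/7.8 = 1.051 | 14.2, so 15 | 15.2 |
| Foot contact time | 104/134 = 0.776 | 26.1, so 27 | 27.06 |

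The stated 27 reproduces as the largest of the three, and foot contact time sets it. By t-test, 27 per group gives 79.9% power.

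**Step 2: the total.** 2 × 34 = 68, whereas 2 × 27 = 54. The printed total is therefore the number before inflation.

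**Step 3: the allowance.**
- As written: 27 × 1.25 = 33.75, rounded to 34.
- Retained after 25% loss: 34 × 0.75 = 25.5, which is 1.5 below 27.
- Correct inflation: 27 / (1 − 0.25) = 36 per group, 72 in total.
- Loss that 34 can absorb: 1 − 27/34 = 20.6%.

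**Step 4: power with 25 or 26 completers per group.**

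| Variable | t-test, n = 25 | t-test, n = 26 | Normal, n = 25 | Normal, n = 26 |
|---|---|---|---|---|
| Foot contact time | 76.7% | 78.4% | 78.4% | 79.9% |
| Single-step threshold | 82.9% | 84.4% | 84.4% | 85.8% |
| Medio-lateral sway | 95.4% | 96.1% | 96.1% | 96.6% |

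For foot contact time the shortfall from 80% is about 0 to 3 percentage points, depending on the formula and on rounding 25.5 down or up. The other two variables stay above 80%.

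**The case against.** **The total is an obvious slip.** This stands. The same sentence gives 34 per group, and two other places give 68. A reader might infer that the protocol leaves two enrolment targets open, or that the wrong total weakens the trial's power. The documents do not support either: every other statement of size agrees on 68, and the 54 enters no later calculation. It still needs correcting, because it stands in the section cited as the justification.

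**The shortfall is trivial and falls on a secondary outcome.** This largely stands. The sentence speaks only of about 25% and about 34, the loss is 1.5 completers per group, and the one primary outcome in the calculation keeps more than 80%. A reader might infer that the trial is underpowered for its primary question, but the document's figures do not show that. What remains is that the formula does not do what the text says it does.

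**Completer power is not the power of the planned analysis.** This stands, and it limits how the step 4 figures may be used. Carrying the last measurement forward keeps all 34 per group in the analysis, and the power of the repeated-measures ANOVA depends on a pre–post correlation that the article does not give. True power could be higher, if baseline and follow-up are well correlated. It could also be lower: if the 25% who drop out carried forward zero change and the standard deviation were unchanged (both assumptions), the effect would shrink to 75% of its size, and t-test power with 34 per group would be about 66% for foot contact time and 73% for the threshold. That is a question about the missing-data method, separate from this point. It does not rescue the arithmetic, since the section presents its own allowance as a replacement for lost participants.

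**Conclusion.** Both errors are certain and can be checked from the article alone. The total should be 68. The factor 1.25 leaves 25.5 per group at 25% attrition, where 27 are required and 36 would have to be randomised; 34 per group covers losses up to about 20%.

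The consequence is minor to moderate. On a two-sample t-test with the document's inputs, 25–26 completers per group give about 77–78% power for foot contact time and 83–84% for the single-step threshold. These figures assume that the stated differences and standard deviations are right, that attrition is equal in the two groups, and that completers alone are compared. They describe the sample-size model and should not be read as the trial's power under its planned analysis. This is a correction to a stated figure, not evidence that the trial is too small.

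**What to change.** Rewrite the last sentence of Sample Size Estimation:

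- Change the total from 54 to 68.
- Replace the claim that 27 × 1.25 allows for 25% attrition. State that 34 per group retains the required 27 at attrition up to about 20%, and that full cover for 25% would need 27/(1 − 0.25) = 36 per group (72).
- Add that at 25% attrition 25–26 completers per group would remain, with power of about 77–78% for foot contact time and 83–84% for the single-step threshold. Label these as completer-based two-sample t-test figures, not the power of the repeated-measures ANOVA with last observation carried forward.
- Name foot contact time, a secondary outcome, as the variable that sets the 27.

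The cost is one reworded paragraph and a slightly less favourable power statement for one secondary outcome. Recruitment and trial conduct do not change. If the sponsor prefers to keep the full 25% allowance, the alternative is 72 participants, four more than planned.

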### Statistical Analysis

PASW Statistics version 26.0 are used for statistical calculations. Baseline characteristics are compared using independent *t*-tests and Mann–Whitney *U*-tests for continuous and ordinal variables, respectively. Descriptive data analysis and tests for the assumptions of normality (Shapiro-Wilk's statistic) are followed by a two-way repeated measure analysis of variance (ANOVA) for within subjects (pre- vs. post-tests) and between groups (experimental vs. control groups). The primary outcome variables are the single-step and multiple-step thresholds, the first-step recovery initiation duration, first step duration, total balance recovery duration, and the MoS. These variables were previously found to be able to distinguish between younger and older adults (14) and between fallers and non-fallers (15). The single-step threshold was previously shown to be an independent predictor of a future fall (16–21) and to reflect unsteadiness in reactive balance control among older adults with varying histories of falls (15). The secondary laboratory outcome variables are foot contact time (voluntary stepping), and the ML CoP sway, as well as SDA parameters (Cd and Ds). All these parameters were previously found to reflect unsteadiness in balance control (13, 50, 55, 56, 58, 67, 68) related to falls (13, 55–58, 60), and also related to older adults who have bicycle riding habits (30). The other secondary outcome measures are the BBS, 6MWT, LLFDI, and FES-I. An intention to treat analysis is conducted by carrying the last obtained measurements forward for those participants who do not complete all aspects of the study. The significance level is *p* < 0.05.

The effect size (ES) (Hedge's g) between the two independent groups is calculated by dividing the difference between the means of each group by the pooled baseline standard deviation of both groups. Values between 0.2 and 0.49 are considered small, between 0.5 and 0.79 moderate, and 0.8 and higher is considered a large effect. In addition, for each outcome parameter, we explore whether a minimal detectable change has been reached. As data will be analyzed at the end of the study, there is no plan for interim analyses of primary and/or secondary variables.

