### Informed Consent

When an older adult is willing to participate in the study, a researcher approaches the subject, schedules a pre-study meeting to explain the study, and provides the study information sheet, information form for the primary care physician, and the permission to participate in the study/consent form. Participants are informed that this is a novel intervention method of a technology that aims to improve balance while riding a new stationary bicycle device, and that we hypothesize that they most likely will improve their function. In addition, they will be informed that both groups will perform bicycle training with or without perturbations thus, both are expected to improve function. To maintain the motivation of older adults to participate, they will be offered to participate in “other” exercise program after the training period. They are also informed that the training might be difficult in the beginning; thus, some muscle soreness will occur, and that participants are free to withdraw from the study at any time point, without consequence. Participants may also be withdrawn from the study due to changes in their health status that affect eligibility. A researcher will answer the participant's questions about the study, and participants may discuss the study with their family members, friends, or healthcare providers. All participants sign an informed consent statement via personal interview at enrollment. The informed consent process is documented by research personnel.

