### Weaknesses

In this study, we aim to improve balance control and balance reactive components by tilting perturbations. However, these tilting perturbations during bicycle riding may not be similar enough to balance loss situations that cause falls among older adults; thus, they may not be specific. Because of the lack of specificity in this model, we may find no effects of the intervention. Perturbations in the experimental group are limited to the ML direction only, while hip balance strategy, which is one target of this training method, are triggered mainly by anterior–posterior movements. Trainers are trained to follow the pedaling intensity according to the training program to control this endurance component in the two intervention groups, but although the bicycle resistance is set equally, it might be difficult to monitor the speed of pedaling for each participant. This program is less challenging than the PBBT in walking and standing, but it is still possible for older adults to have difficulties in hands-free riding or to progress very slowly in the training program, which may not be enough to lead to improvement. Lastly, since the PBBT is a challenging training approach, there is a risk that older adults will stop participating in the program (drop out). In regard to our RCT study, there are disadvantages (limitations) to the convenience sampling that may weaken this study. The convenience sampling can lead to the under-representation or over-representation of particular groups within the sample. For example, old volunteers that commits to train 3 months are different from the general population of older adults. This undermines our ability to generalize our results to the general population of older adults. However, in our RCT the participant is randomly allocated to two groups thus a significant improvement in balance control system in one of the groups may truly represent a change in the balance function.

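### The planned pre/post ANOVA gives a valid between-group test but leaves the baseline value unused as a covariate; ANCOVA on T2 would be more precise at no cost, and one sentence under Weaknesses needs rewording

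*Protocol article*

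**What the plan says.** - **Model.** Statistical Analysis describes a "two-way repeated measure analysis of variance (ANOVA) for within subjects (pre- vs. post-tests) and between groups (experimental vs. control groups". The time and group factors are named. The term that carries the treatment effect is not singled out, and no covariate is listed.
- **Use of T1.** Each outcome is measured once before training (T1) and once after 12 weeks (T2). Apart from being the pre-test level of the ANOVA, T1 data serve for baseline group comparisons and for the standard deviation in Hedges' g.
- **Effect size.** Hedges' g is obtained by "dividing the difference between the means of each group by the pooled baseline standard deviation of both groups". The text does not say whether these means are T2 values or changes from T1.
- **Interpretation.** Weaknesses, after discussing convenience sampling, says that because participants are randomised "a significant improvement in balance control system in one of the groups may truly represent a change in the balance function".
- **Expected course.** Informed Consent tells participants that "both are expected to improve function", and Strengths likewise expects both groups to gain.

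**The concern.** Two things are at stake.

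The first is precision. A repeated-measures ANOVA with one pre-test and one post-test treats T1 as an outcome and in effect subtracts it in full. ANCOVA subtracts only the part of T1 that predicts T2, so its standard error is smaller whenever r is below 1. In a trial sized at 27 completers per group, that can decide whether the planned power is reached.

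The second is interpretation. If both arms are expected to improve, a significant improvement in one arm says nothing specific about perturbations. Randomisation justifies comparing the arms, not reading one arm's change on its own.

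**Working it through.** **Inputs (Sample Size Estimation).** Differences: "Using net reduction values (2.9 cm, 8.2 mm, and 104 ms, respectively"). Spread: "standard deviations of 3.45 cm, 7.8 mm, and 134 ms, respectively". Error rates: "Type I error probability of 0.05 and Type II error probability of 0.2 was applied for the three two-sided test calculations". The three outcomes are the single-step threshold (primary), mediolateral sway and foot contact time (both secondary). Stated result: 27 per group.

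**Step 1: reproduce the plan's figure.** n per group = 2 × (1.960 + 0.842)² × (SD/difference)².
- Single-step threshold: 15.70 × (3.45/2.9)² = 22.2, so 23.
- Sway: 15.70 × (7.8/8.2)² = 14.2, so 15.
- Foot contact time: 15.70 × (134/104)² = 26.1, so 27.

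The largest is 27, as stated. Foot contact time drives it. No pre-post correlation enters.

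**Step 2: variances.** Assume equal SD at T1 and T2, and correlation r. In units of SD²:
- group-by-time contrast (change score): 2(1 − r)
- ANCOVA of T2 on T1: 1 − r²
- ratio of ANCOVA to change score: (1 − r²)/[2(1 − r)] = (1 + r)/2

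The ratio is 0.65, 0.75, 0.85 and 0.90 at r = 0.3, 0.5, 0.7 and 0.8. The variance is therefore 35%, 25%, 15% and 10% lower with ANCOVA.

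**Step 3: power at 27 per group** (two-sided t-test, alpha 0.05; the one degree of freedom spent on the covariate is ignored). The standardised difference is d/√[2(1 − r)] for the interaction and d/√(1 − r²) for ANCOVA.

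| Outcome | r (assumed) | Interaction | ANCOVA |
|---|---|---|---|
| Single-step threshold, d = 2.9/3.45 = 0.841 | 0.3 | 72.6% | 88.8% |
| | 0.5 | 85.8% | 93.8% |
| | 0.7 | 97.5% | 98.9% |
| Foot contact time, d = 104/134 = 0.776 | 0.3 | 65.7% | 83.5% |
| | 0.5 | 79.9% | 89.8% |
| | 0.7 | 95.1% | 97.5% |

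**Step 4: is the planned interaction test valid?** In 20,000 simulated trials with no treatment difference and a common gain of 0.3 SD, it rejected in 5.1% (r = 0.5) and 4.8% (r = 0.7). Its type I error is correct.

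**Step 5: the one-group inference.** Assume no treatment difference, a common gain of 0.2 to 0.3 SD, r of 0.5 to 0.7 and 27 per arm. A paired t-test in one arm has noncentrality gain × √27/√[2(1 − r)]. The experimental arm then improves significantly in 17% to 49% of trials, and does so while the control arm does not in 14% to 25%. These gains are illustrative; the protocol gives none. In the Step 4 simulations the time main effect was significant in 58% (r = 0.5) and 80% (r = 0.7) of trials.

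**The case against.** The strongest reply is that the plan contains no error. The ANOVA sentence names the two factors of the design; it does not say that main effects will be tested as the treatment effect. A mixed two-way ANOVA reports the group-by-time interaction as standard output, and a condensed article may leave the naming of that term to a fuller document. This stands. A reader might infer that the plan tests main effects only, but the text does not say so. The low power of a group main effect, which averages T1 and T2, is therefore not a fair charge against it.

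A reader might also infer that leaving T1 out as a covariate biases the result or raises the error rate. It does neither. Under randomisation the change-score comparison is unbiased and holds its 5% level. What is lost is precision, together with some protection against chance baseline imbalance.

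The Weaknesses sentence could be read as a decision rule. It is a hedged remark about convenience sampling, and other text points to a between-arm comparison: Hedges' g is defined between the two groups, and the sample size rests on a two-group difference. The consent wording concerns function in general, not the reactive-balance outcomes specifically. What remains is that the inference, as written, is unsound when both arms are expected to improve.

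Finally, the size of the gain depends on an r that the protocol does not supply.

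**Conclusion.** The point holds as an efficiency improvement plus a wording correction, not as a validity defect. The planned interaction test is sound. Adjusting T2 for T1 would lower the variance by 10% to 35% for assumed r between 0.8 and 0.3.

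For the primary single-step threshold this is worth about 16, 8 and 1 percentage points of power at r = 0.3, 0.5 and 0.7. For foot contact time it is about 18, 10 and 2 points. With the interaction test, foot contact time falls below the planned 80% only when r is below about 0.5; ANCOVA exceeds 80% at every r examined. At r of 0.7 or above the choice hardly matters.

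These figures assume equal SDs at T1 and T2, that the quoted SDs describe single measurements rather than changes, and 27 analysed per group. The conclusion about the Weaknesses sentence needs no numerical assumption: it follows from the protocol's own expectation that both groups improve.

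**What to change.** 1. In Statistical Analysis, state that for each outcome analysed as continuous, the treatment effect is the between-group difference at T2 from an ANCOVA with the T1 value as covariate, reported with a 95% confidence interval.
2. Compute Hedges' g from that adjusted difference, keeping the pooled baseline SD as divisor. This also settles which means are used.
3. Report the time effect and within-group changes descriptively only.
4. Reword the last sentence of Weaknesses so that a conclusion about perturbation training rests on the between-group difference, not on significant improvement in one group.

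The cost is a few sentences. No extra measurements or participants are needed, and T1 is already collected.
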